## Abstract

**Background:**

Different non-pharmacological techniques, including hypnosis and virtual reality (VR) are currently used as complementary tools in the treatment of anxiety, acute and chronic pain. A new technique called virtual reality hypnosis (VRH), which encompasses a combination of both tools, is regularly used although its benefits and underlying mechanisms remain unknown to date. With the goal to improve our understanding of VRH combination effects, it is necessary to conduct randomised and controlled research trials in order to understand their clinical interest and potential benefits.

**Methods:**

Patients (n = 100) undergoing cardiac surgery at the Liège University Hospital will be randomly assigned to one of four conditions (control, hypnosis, VR or VRH). Each patient will receive two sessions of one of the techniques: one the day before the surgery and one the day after. Physiological assessments will be made on the monitor and patients will rate their levels of anxiety, fatigue, pain, absorption and dissociation.

**Discussion:**

This study will help to expand knowledge on the application of virtual reality, hypnosis and VRH in the specific context of cardiac and intensive care procedures, and the influence of these non-pharmacological techniques on patient’s anxiety, fatigue, pain and phenomenological experience.

**Trial registration:**

ClinicalTrials.gov: NCT03820700. Date registered on 29 January 2019.

Study recruitment date: October 6, 2018. Study anticipated completion date: December 28, 2020.

## Background

The aim of this study is to better understand the use of non-pharmacological approaches to reduce anxiety among patients in intensive care units (ICUs), and their potential clinical benefits in one specific population of patients, i.e. patients undergoing cardiac surgery.

Anxiety, pain and fatigue are important factors influencing the recovery of patients after surgery. The definition of preoperative anxiety is “an unpleasant state of uneasiness or tension that is secondary to a patient being concerned about a disease, hospitalization, anaesthesia and surgery, or the unknown” [1]. Among patients admitted to hospital for surgery, 20–28% reported high preoperative anxiety and 60% reported minimal anxiety in two studies investigating this issue [2, 3]. Patients’ anxiety before surgery is a risk for postoperative recovery problems and its consequences are of paramount importance in delaying wound healing [4]. In addition, preoperative anxiety is reported to significantly influence the intensity of postoperative pain [5, 6]. Studies have shown that among patients in the ICU, pain is associated with an unpleasant stay, sleep deprivation, increased agitation, high rates of post-traumatic stress disorder and feeling unsafe in the ICU environment [7–13].

Currently, pharmacological treatments for anxiety and pain are well-developed in the ICU environment, where pain and fatigue are most commonly managed by opioid analgesics, propofol and benzodiazepines [14]. Pharmacological treatment could be considered efficient when the patient feels comfortable, with no adverse effects [15]. Yet, opioid analgesics (e.g. morphine) often lead to respiratory sedation, hyperalgesia, depression, nausea, opioid-induced tolerance and dependence [15]. Benzodiazepines can be used in the short term but can lead to strong dependence, with important adverse effects: ataraxia, irritability, nervousness, depression and risk of suicide [16]. Further, some pharmacological interventions (e.g. lorazepam and pregabalin), intended to treat anxiety, fail to decrease preoperative anxiety and postoperative pain [17, 18]. In the ICU environment, deep levels of sedation potentially lead to increased mortality and lengths of stay [19]. In the light of this, non-pharmacological approaches are of interest as complementary techniques to reduce anxiety and pain. Techniques such as hypnosis and virtual reality (VR) have been investigated in numerous studies in the medical field (e.g. algology, oncology, anaesthesia) to reduce pain and anxiety and increase patients’ comfort [20–22]. Hypnosis is defined as a “state of modified consciousness involving focused attention and reduced peripheral awareness, characterized by an enhanced capacity for response to suggestions” [23]. Hypnosis has three main components: absorption, dissociation and suggestibility. Absorption is the tendency to become fully involved in a perceptual, imaginative or ideational experience; dissociation is the mental separation from the environment; and suggestibility is the responsiveness to social cues, leading to an enhanced tendency to comply with instructions and a relative suspension of critical judgment [24]. This technique is considered safe, and one that allows the patient to be focused on his or her inner world, by including cognitive and behavioural components that enable the mind to influence body sensations and perceptions [25–27]. Hypnotic suggestions can be used to modify perception of symptoms such as pain, anxiety and fatigue, in different health-related disorders (e.g. oncology, chronic pain, surgery). In some cases, hypnosis can be a complement to other medication therapy to reduce anxiety before surgery (e.g. presurgical anxiety in coronary artery bypass and cataract surgery) [28–30] and also after surgery (e.g. during weaning from mechanical ventilation) [31]. A recent meta-analysis showed that hypnosis is a highly effective intervention for anxiety and is more effective when combined with other psychological interventions and various clinical applications [28]. Hypnosis is known to reduce acute and chronic pain [32–36] and improve sleep quality [37, 38]. A variety of relaxation techniques have been investigated to improve the quality of sleep in ICU patients (e.g. aromatherapy, earplugs and masks, noise bundle) but results are not convincing in all studies [39, 40]. One review of the literature showed that hypnosis seems to be a promising technique for management of sleep problems; however, more randomised studies are required to support these results [34]. Hypnosis is an efficient treatment in health care, and one that can save time and costs to healthcare providers in some instances [35, 41].

There has been growing interest in the use of virtual reality (VR) in medicine [20]. VR involves computer-generated, immersive and three-dimensional technologies. VR subjective experience is characterized by senses of immersion and presence. Presence refers to the degree to which the subject experiences being in the virtual environment [42, 43], while immersion is the amount of sensory input the VR system creates [44]. Feedback systems with trackers - and often helmet and gloves - allow individuals to be distracted by interacting with a virtual world and make it as “real” as possible [45]. According to Patterson et al. (2006), immersion in VR can isolate the patient from the outside environment and it is effective in distracting the subject’s attention from a painful stimulus [46, 47]. VR has been shown to divert attention from painful stimulation in both highly hypnotizable and less hypnotizable individuals in experimental and clinical settings [48, 49]. VR can also be considered as an efficient non-pharmacological tool to decrease anxiety (e.g. during dental treatment or phobia therapy) [50, 51]. In our experiment, VR is not used during a painful stimulus but before and after a painful and stressful intervention, i.e. surgery. VR distraction is an adjunctive tool to clinical interventions for such issues as acute and chronic pain management, clinical education, cognitive and motor rehabilitation, anxiety management and communication skills training; however, less is known about its efficacy in decreasing fatigue [20, 52].

Virtual reality hypnosis (VRH) is a technique that combines VR hardware/software and hypnotic induction followed by analgesic suggestions [53]. According to Patterson et al. (2004; 2010), “VRH uses a high-resolution, head-mounted display that delivers absorbing visual images and high-fidelity audio that provide an induction […] followed by suggestions for comfort and pain relief” [53, 54]. Studies have demonstrated positive effects of VRH on pain and anxiety [48], but the actual mechanisms of this treatment are not well-known. Hence, it seems that even if immersion is present in VRH and hypnosis, it would not necessarily bring about the same effects as it does with VR distraction. For example, in hypnosis, absorption and dissociation come from the subject who constructs his own world with the hypnotherapist’s suggestions. In VR, that world is imposed on the subject with existing technology. To our knowledge, two randomised studies have previously been conducted to compare hypnosis, VR and VRH in experimental setups [47, 48]. However, there is a need to compare the efficiency of these techniques in clinical practice.

One of the main goals of caregivers is to create the best environment for reducing the patient’s anxiety in surgery and in the ICU by using the patient’s own resources. In this study, we wish to compare three non-pharmacological methods in patients undergoing cardiac surgery and hospitalized in the ICU: hypnosis, VR and VRH. By comparing these non-pharmacological tools, we would be able to better understand their relative efficacy and mechanisms in making the patient more comfortable. Randomised, controlled research trials are necessary to evaluate how the patient’s cognition and perception of these tools can impact the outcomes [20, 26].

## Methods/design

### Aim

The aim of the project is to better understand the impact of VR, hypnosis and VRH on individual perception and sensation in patients hospitalized in cardiac surgery and ICU departments. The primary outcome will be patients’ anxiety levels preoperatively and in postoperative recovery. Secondary assessments will include assessment of pain, fatigue, relaxation, physiological parameters, absorption, dissociation and presence concepts.

### Study registration

This study has been approved by the Ethic Committee of the Faculty of Medicine and the Ethic Committee of the Faculty of Psychology, Speech Therapy and Educational Sciences of the University of Liège. This trial was registered on clinicaltrials.gov with the trial identification number NCT03820700 in January 2019. The trial is currently ongoing and recruiting.

### Eligibility criteria

This study will have a prospective randomised design, and will be a single-centre trial with four arms, including three experimental and one control group. The study sample will comprise adult patients undergoing cardiac surgery (coronary artery bypass graft; mitral heart valve replacement; aortic valve replacement; others). All the study procedures and surgery will be conducted in the University Hospital of Liège (Belgium). Informed consent will be obtained before inclusion of patients.

There will be 100 patients included in the study (25 patients per condition). The participants will be adults undergoing cardiac surgery who have provided informed consent for their participation in the study. This choice is due to the high prevalence of patients undergoing cardiac surgery and accessibility to these patients at the university treatment centre, and the possibility of easily collecting physiological data and patients’ reports. The age of the patients will range from 18 to 90 years. Patients have to be conscious, awake and able to understand and answer in fluent French. Exclusion criteria are psychiatric diseases like dementia, claustrophobia, acrophobia, severe hearing problems, visual impairment or a state of confusion (Table 1).

**Table 1 Tab1:** Study inclusion and exclusion criteria

Inclusion criteria are:	
- Adults > 18 years of age	
- French-speaking	
- Undergoing cardiac surgery	
- Provision of written consent for their participation	
Exclusion criteria are:	
- Psychiatric diseases	
- Claustrophobia	
- Acrophobia	
- Severe hearing impairment	
- Visual impairment	
- Surgery cancelled or postponed	
Postoperative dropout criteria are:	
- Death during surgery	
- Refusal to continue the study	
- Extreme fatigue	
- Verbal incoherence	
- State of confusion	
- Glasgow Coma Scale [55] score < 14 - Richmond Agitation-Sedation Scale [56] 1 > score < − 1	

### Design

Participants will be randomly included in the following conditions:
Control group: daily care only.Hypnosis: taped hypnosis called “Soothing white clouds”.

The hypnosis session will consist of a 20-min hypnosis recording created by [name] and [name], both experts in clinical and experimental hypnosis. The recording, named “Soothing white clouds”, includes suggestions about relaxation, positive body sensations and invitation to observe a sunrise and a beautiful landscape, while relaxing in a white cloud chair. Suggestions are focused on variables we wish to improve with the patient (i.e. relaxation) and not on symptom relief. An example of the text (the original text is in French) is as follows: “This experience invites you to discover your resources to find more comfort, calm and healing… I suggest you to find a comfortable position to take full advantage of this moment […] You can discover new perspectives in this soothing white clouds, note others details, and appreciate to be present in this moment […] appreciate the air around you, breathing oxygen, this energy source, which give energy to your body, everywhere it’s needed…”
3.Virtual reality (VR): mountain landscape 3D animation and sounds of nature

For the VR session we will use a head-mounted 3D graphical display with goggles. This VR environment consists of visualization of a landscape accompanied by sounds of nature. The 3D immersive landscape features a shed near a lake at sunrise followed by a relaxing moment in the clouds. This device was constructed by Oncomfort© according to what we wish the patient to visualize in the hypnosis condition (i.e. landscape, sunrise, clouds). The session lasts 20 min and ends on the lake’s edge. There is no verbal suggestion in this VR device. Sounds consist of water sound, birds and the cicada’s song. Participants will not interact with the environment; they are invited to simply watch the 3D animation and relax during the session.
4.Virtual reality hypnosis combination (VRH): mountain landscape 3D animation plus taped hypnosis “Soothing white clouds”.

In VRH, we replace the sounds of nature used for the VR device by the hypnotic tape in order to have the ideal experimental conditions to compare the techniques. The *Soothing white clouds* hypnosis session is combined with a 3D visual movie (immersive landscape and relaxing moment in the clouds (Oncomfort©)), with a duration of 20 min. The text for hypnosis is the same as in the hypnosis group and includes suggestions about relaxation, positive body sensations, invitation to observe a sunrise and a beautiful landscape, while relaxing in a white cloud chair. The hypnosis script was previously recorded (see hypnosis group description) and then integrated into the VR device. In that way, participants can listen to the hypnosis record throughout the VR session.

Initial contact between the investigator and the patient will take place in the patient’s room one day before cardiac surgery. The investigator will request each patient to consent for participation in the study and subsequently record their demographic data (age, gender, surgery type, alcohol and tobacco use). Hypnosis, VR or VRH will be applied in 20 min session: the day before surgery (day − 1 at 5.00 p.m.) and the day after surgery (day + 1 at 2.00 p.m.). Before and after each session, physiological measurements will be recorded (heartbeat, arterial pressure), and a visual analogical scale (VAS) will be used to assess anxiety, fatigue, pain and relaxation. The VAS is a continuous scale subjectively assessed by the patient and ranges from 0 (no pain/anxiety/fatigue/relaxation) to 10 (maximum pain/anxiety/fatigue/relaxation). We ask the patients to assess their “current pain intensity/anxiety/fatigue/relaxation at the moment”. This score determines the intensity of these variables at a given time [57]. After the session, patients will complete questions about absorption and dissociation (Table 2).

**Table 2 Tab2:** Standard Protocol Items: Recommendation for Interventional Trials (SPIRIT) study schedule

Timepoint	Study period				
	Hospital admission (Day − 1)		Surgery (Day 0)	Intensive care unit admission (Day + 1)	
	***T0***	***T1***		***T2***	***T3***
**Enrolment**					
Eligibility screen	**X**				
Informed consent	**X**				
**Allocation**					
Control, hypnosis, virtual reality, virtual reality hypnosis	**X**				
**Assessments**					
**Baseline:** demographic factors, Dissociative Experience Scale [58]	**X**				
**Primary outcome:** anxiety	**X**	**X**		**X**	**X**
**Secondary variables**: pain, fatigue, relaxation, heart rate, arterial pressure, respiratory rate, oxygen saturation, pupil size	**X**	**X**		**X**	**X**
**Phenomenology scales**: absorption, dissociation, immersion, presence, time perception		**X**			**X**
Nurse’s and patient’s interview		**X**			**X**

### Recruitment and randomisation

Each patient scheduled for cardiac surgery who meets our exclusion and inclusion criteria will be asked to participate. The number of patients who refuse to participate will be recorded, and demographic data will be collected to allow a comparison with those who participate. Written informed consent will be obtained before inclusion. The selected patients will be randomly assigned to one of the four groups, using block randomisation with a block size of 5 to obtain a good balance of participants between the four groups during the recruitment period. The recruitment started in October 2018 and is ongoing. Sample size has been determined by a power analysis calculated to detect a difference in the evolution of data between the four groups. The sample size calculation was based on repeated measures analysis of variance (ANOVA). Alpha was set at 0.05, power at 95% and the standardized effect size at 0.5. In other studies designed to assess the effect of hypnosis on patients’ anxiety pre-surgery, an effect size of 0.2 has been considered small, 0.5 moderate and 0.8 large [29]. According to this analysis, 12 patients are required in each group giving a total of 48 patients. We decided to enrol 100 patients (25 per group) at day 1 to compensate for dropouts on the day after surgery (Fig. 1).

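### A single fixed block of 5, in one centre with visibly different arms, makes the next allocation partly foreseeable to anyone who knows the block length and sees past allocations (minor)

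*Protocol article*

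**What the plan says.** - **Allocation.** The Recruitment and randomisation section states one block length for the whole trial, "using block randomisation with a block size of 5 to obtain a good balance of participants" across the four groups. It mentions no varying lengths and no stratification, and does not say how five places are shared among four arms.
- **Setting.** The Eligibility criteria section describes a "single-centre trial with four arms, including three experimental and one control group", with 100 patients, 25 per condition.
- **Arms.** The Design section lists "Control group: daily care only", a hypnosis recording, a head-mounted display, and the display with the recording. The article does not discuss masking, but these arms cannot look alike to whoever delivers or observes them.
- **Enrolment.** In the Design section, "The investigator will request each patient to consent for participation in the study", at first contact on the day before surgery. Table 2 puts eligibility screen, consent and allocation at the same timepoint, T0.
- **Safeguards.** The Recruitment and randomisation section also says "Each patient scheduled for cardiac surgery who meets our exclusion and inclusion criteria will be asked to participate". Refusals are counted, and demographic data are collected to compare those who refuse with those who take part.
- **Status.** Recruitment began in October 2018 and was still under way when the article gave the block length.

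**The concern.** With one centre and no strata, the blocks are simply patients 1 to 5, 6 to 10 and so on, so block boundaries can be found by counting. Because the arms are visible in use, past allocations can be known. A known short block plus known past allocations narrows down the next arm. Concealing the list does not prevent this, because the information comes from the scheme and not from the list.

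Foreknowledge at the moment of seeking consent would let enrolment depend on the coming arm, through judgement-based entry criteria (psychiatric disease, severe hearing impairment) or through the manner of approach. The primary outcome is self-rated anxiety, so arms could come to differ in the kind of patient enrolled. The Discussion names the randomised controlled design as a particular strength, and this choice weakens it for no gain in sample size or effort.

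**Working it through.** **Inputs from the article:** block length 5, four arms, one centre, 25 per arm.

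**Assumptions:** the observer knows the block length, the composition rule, the block boundaries and all past allocations. Each block holds every arm once plus one arm repeated at random. The article states none of these.

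**Step 1. Best guess at each place in a block of 5.** Each arm is the repeated one with prior probability 1/4. That prior is updated by the allocations seen so far in the block.

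- Place 1: 1/4 = 0.250.
- Place 2: the arm just seen has weight 2 as the repeat, each other arm weight 1 (sum 5). An unseen arm has probability (2·1/4 + 1·2/4 + 1·1/4 + 1·1/4)/5 = 0.300.
- Place 3: the first two places share an arm with probability 1/10, and the best guess is then 1/3. Otherwise (9/10) the weights are 2, 2, 1, 1, and an unseen arm has (4·1/3 + 2/3 + 1/3)/6 = 7/18. Average: 0.1·1/3 + 0.9·7/18 = 0.383.
- Place 4: both copies of the repeated arm have appeared with probability 3/10, which leaves two arms at 1/2 each. Otherwise (7/10) the one unseen arm has (6·1/2 + 1)/7 = 4/7. Average: 0.3·1/2 + 0.7·4/7 = 0.550. The best guess is at least 50% likely in every case.
- Place 5: both copies have appeared with probability 6/10, and the missing arm is then certain. Otherwise (4/10) all four arms have been seen once and each has 1/4. Average: 0.6 + 0.4·1/4 = 0.700.

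**Step 2. Totals for the block of 5.**

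- Certain places: 0.6/5 = 12%, about 12 of 100 patients.
- Places at least 50% likely: (1 + 0.6)/5 = 32%.
- Correct best guesses: (0.250 + 0.300 + 0.383 + 0.550 + 0.700)/5 = 2.183/5 = 43.7%, against 25% by chance.

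**Step 3. Other readings of the block.**

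- Repeated arm fixed and known: place 5 is always certain, and place 4 is certain when both copies are still to come (probability 1/10). Certain places: (1 + 0.1)/5 = 22%. Correct guesses: 55.7% (simulation).
- 5 meaning five per arm, that is, blocks of 20: 6.3% certain, 40.6% correct (simulation).

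**Step 4. Alternatives, same observer.** The fixed 4 is exact: one place in four is certain, and correct guesses are (1/4 + 1/3 + 1/2 + 1)/4 = 52.1%. The other alternatives are simulated. For the mixed lengths, the observer knows the possible sizes but not the boundaries.

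| Scheme | Certain places | Correct best guesses |
|---|---|---|
| Fixed 5, random repeat | 12% | 43.7% |
| Fixed 4 | 25% | 52.1% |
| Random 4/8 | 7.5% | 48.7% |
| Random 12/16/20 | 1.8% | 41.1% |
| One list of 100 | 1.3% | 32.6% |

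The gain from one list depends on how many places remain. Correct guesses are about 33% with 100 places, 37% with 40 and just over 40% with 20 (a balanced list of 20 is the same as one block of 20, 40.6%).

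**The case against.** - **The mechanism needs facts that the article does not give.** The enroller would have to know the block length, composition and past allocations, and act on them. Who holds the list and what enrollers are told is usually left to the full protocol, so that silence is not a fault. This stands, and it makes the point a risk rather than a demonstrated bias. It does not remove the point, since the short fixed block is a stated choice.
- **The article limits selection.** Every eligible patient is asked, refusals are recorded and compared, and first contact is the day before scheduled surgery, which leaves little room to hold a patient for a preferred slot. This stands in part. Judgement of eligibility and manner of approach remain open, and the comparison with refusers is on demographic data, not anxiety.
- **A reader might infer that a large share of allocations is known in advance.** The figures do not support that. About 12% are certain on the literal reading. On the five-per-arm reading it is 6.3%, and the guess rate (40.6%) is already level with the 12/16/20 scheme (41.1%).
- **A reader might also infer a bias of about half a VAS point in the result.** Suppose an enroller acts whenever an arm is at least 50% likely, taking patients 1 point calmer before VRH and 1 point more anxious before control. The two arms then differ by about 0.45 points. That is a difference in level, produced by assumed behaviour, and it would already be visible at T0. The Statistical analysis section compares the evolution of scores between groups and adjusts for potential confounders. A shift that persists equally from T0 to T3 adds nothing to that comparison. Indirect routes such as regression to the mean or floor effects remain, but nothing in the article allows them to be sized.

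**Conclusion.** The point holds as a minor weakness in a stated design choice. On the literal reading with a random repeat, 12% of places are certain, 32% are at least 50% likely and best guesses succeed 44% of the time. Across readings of the unstated composition, certain places range from 6% to 22% and correct guesses from 41% to 56%. All these figures assume an observer who knows the scheme and the past allocations. Masking is not mentioned; that the arms are distinguishable is inferred from what they are. The resulting bias is zero if nobody acts on the foreknowledge, and the documents do not support putting a VAS figure on its effect on the planned result. Action is still worthwhile because the remedy is cheap.

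**What to change.** For the places still open, replace the fixed block of 5 by one of the following:

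1. one computer-generated permuted list that brings each arm to 25; or
2. if balance over calendar time is wanted, longer randomly varying blocks in multiples of four (for example 12, 16 and 20), with lengths not disclosed to those who enrol.

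Do not simply shorten the block to 4. That makes the blocks divisible by four arms but about doubles the certain places, from 12% to 25%. Mixing 4 and 8 cuts the certain places but raises correct guesses to 48.7%.

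For patients already randomised, state how the blocks of 5 were composed. For all patients, report T0 anxiety by arm.

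**Cost:** a new list for the remaining patients and one changed sentence, with no extra patients or staff. Balance between arms over calendar time becomes somewhat looser. Arms end at 25 with the single list, and differ by about 1 to 2 patients on average with the varying blocks. The benefit shrinks as fewer places remain. The varying blocks mainly remove certain places (12% to 1.8%) and lower the guess rate only slightly (43.7% to 41.1%). If recruitment is complete, only the reporting items apply.
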